## Abstract

**Introduction:**

Chronic breathlessness is a common and debilitating symptom, associated with high healthcare use and reduced quality of life. Challenges and delays in diagnosis for people with chronic breathlessness frequently occur, leading to delayed access to therapies. The overarching hypothesis is a symptom-based approach to diagnosis in primary care would lead to earlier diagnosis, and therefore earlier treatment and improved longer-term outcomes including health-related quality of life. This study aims to establish the feasibility of a multicentre cluster randomised controlled trial to assess the clinical and cost-effectiveness of a structured diagnostic pathway for breathlessness in primary care.

**Methods and analysis:**

Ten general practitioner (GP) practices across Leicester and Leicestershire will be cluster randomised to either a structured diagnostic pathway (intervention) or usual care. The structured diagnostic pathway includes a panel of investigations within 1 month. Usual care will proceed with patient care as per normal practice. Eligibility criteria include patients presenting with chronic breathlessness for the first time, who are over 40 years old and without a pre-existing diagnosis for their symptoms. An electronic template triggered at the point of consultation with the GP will aid opportunistic recruitment in primary care. The primary outcome for this feasibility study is recruitment rate. Secondary outcome measures, including time to diagnosis, will be collected to help inform outcomes for the future trial and to assess the impact of an earlier diagnosis. These will include symptoms, health-related quality of life, exercise capacity, measures of frailty, physical activity and healthcare utilisation. The study will include nested qualitative interviews with patients and healthcare staff to understand the feasibility outcomes, explore what is ‘usual care’ and the study experience.

**Ethics and dissemination:**

The Research Ethics Committee Nottingham 1 has provided ethical approval for this research study (REC Reference: 19/EM/0201). Results from the study will be disseminated by presentations at relevant meetings and conferences including British Thoracic Society and Primary Care Respiratory Society, as well as by peer-reviewed publications and through patient presentations and newsletters to patients, where available.

**Trial registration number:**

ISRCTN14483247.

Strengths and limitations of this studyA mixed methods approach will be used to both understand how breathlessness is perceived and diagnosed in primary care, and further interpret the findings of the feasibility study.The structured diagnostic pathway uses existing investigations available in primary care which will aid future implementation.The trial is embedded within clinical care and uses opportunistic recruitment when patients present with breathlessness in primary care.The study design is a cluster randomised trial to minimise potential bias and contamination.The trial will be conducted in a single region in the UK and may limit the generalisability of the study findings.

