### Trial design and registration

This is a 1-year feasibility cluster RCT recruiting from primary care. Ten GP practices from East and West Leicestershire and Leicester City clinical commissioning groups (CCG) will be cluster randomised to a structured diagnostic pathway or usual care. The intervention practices will follow a structured diagnostic pathway to include early investigations. Usual care will continue without any intervention.

The University of Leicester will act as study sponsor and the trial has been registered on the ISRCTN website.

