#### Eligibility criteria for GP practices

GP practices will be approached to take part in this study if they serve a patient population over 10 000. Practices that are research active, as identified by the local Clinical Research Network research scheme, will be approached. The practices will be visited by the study team to discuss taking part in the study and engage with the practice teams.

The GP practices will be randomised 1:1 and stratified by CCG using Statarand,^25^ a Stata randomisation module (Boston College Department of Economics).

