#### Recruitment

Patients will be recruited over 1 year. Patients who meet the above eligibility criteria will be approached in primary care when they present with symptoms of chronic breathlessness. An electronic template on the patient record, triggered at the point of consultation, will be used to aid opportunistic recruitment (see figure 1). The template will be triggered by either free text or Read codes relating to breathlessness. Limits have been set on the trigger to avoid it appearing for patients who have an existing diagnosis of COPD or HF. The template summarises the study, prompting the GP to ask if the patient gives consent to be contacted by the study team. The GP will select yes or no as appropriate to the patient agreeing to have their contact details sent to the study team.

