#### Procedure

A weekly search will be performed by practice staff to provide a report of patients who have agreed to be contacted by the study team following discussion with the GP, as described above. The report will be sent via secure encrypted nhs.net email and patients will be contacted to complete telephone screening for eligibility. A script for telephone screening will be available for use to confirm patients’ age, previous medical history and to explain the study in more detail. If patients agree to hear more about the study they will be sent a participant information sheet by post and, where willing, a provisional appointment letter. When patients attend their research visit, they will complete written informed consent (online supplemental file 1) and their GP will be notified of their involvement in the study. For patients who decline to take part in the study or are ineligible, the reasons will be documented and collated.

10.1136/bmjopen-2021-057362.supp1Supplementary data

Where possible, patients will attend their research visit within 1 month of seeing the GP with their breathlessness symptoms. Patients will attend a second research visit 12 months after their initial appointment and also be contacted by phone at 6 months and asked to complete the questionnaire pack, which will be sent in the post. Please see figure 2 for the study schedule.

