### Intervention—structured diagnostic pathway

Patients who attend GP surgeries in the intervention group will undergo a set of investigations within 1 month; body mass index (BMI), spirometry, ECG, chest X-ray, full blood count, N-terminal (NT)-pro hormone brain natriuretic peptide (NT-proBNP) profile, anxiety and depression screening using the Patient Health Questionnaire—4 item (PHQ-4)^27^ and the General Practice Physical Activity Questionnaire.^28^ The GPs and clinicians will be provided with the pathway document to support a structured history, examination and use of the investigations (figure 3). The electronic template will prompt the GP to action these investigations. The pathway will also be provided as a laminated document for each clinician in the intervention practices, with small laminated flash cards of the investigations available on the work station. The pathway will recommend that patients are reviewed, along with their results, within 1 month and appropriate next steps to be taken regarding patient management.

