**Figure 3 F3:**
[figure not shown]
Diagnostic pathway. BNP, brain natriuretic peptide; BP, blood pressure; COPD, chronic obstructive pulmonary disease; FBC, full blood count; FEV1, forced expiratory volume in 1 s; FVC, forced vital capacity; GPPAQ, General Practice Physical Activity Questionnaire; HR, heart rate; JVP, jugular venous pressure; MRC, Medical Research Council; PHQ-4, Patient Health Questionnaire 4; PND, paroxysmal nocturnal dyspnoea; PRISM, Patient and Referral Implementation SysteM; RR, respiratory rate; TSH, thyroid stimulating hormone.

Usual care will also have the electronic template triggered but will only ask the patient for their consent to pass on contact details to the study team. The GPs and clinicians in usual care will be asked to proceed with investigating the patient and their symptoms as per their usual practice and be directed to the NICE Clinical Knowledge summary for breathlessness^14^ to standardise care.

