#### Data analysis

Data analysis will be performed in an exploratory fashion. Descriptive statistics, number and percentage for categorical data and mean and SD or median and IQR for non-normally distributed continuous data will be present for all demographics, baseline characteristics and questionnaire scores. Normality of the baseline characteristics will be determined using the Kolmogorov-Smirnov test or Shapiro-Wilk test depending on final recruitment numbers.

SPSS V.26 will be used for statistical analysis. GraphPad software will be used for any figures. Data analysis will be performed on the complete data set using all participants.

Secondary outcomes for both groups will be described as mean (SD) and median (IQR) for normally or non-normally distributed data, respectively. The time to diagnosis will be analysed using survival analyses based on Cox proportional hazards survival modelling. The proportion of patients with valid diagnosis at 3 months and 1 year will be described and compared using χ^2^ tests.

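### Cluster randomisation is credited with minimising bias, but GPs who can see their arm recruit patients after allocation, so it limits contamination and not recruitment bias

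*Protocol article*

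**What the plan says.** The strengths and limitations list after the abstract states: "The study design is a cluster randomised trial to minimise potential bias and contamination".

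The rest of the article describes how patients enter the trial:

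- **Allocation.** Under Trial design and registration, "Ten GP practices from East and West Leicestershire and Leicester City clinical commissioning groups (CCG) will be cluster randomised". Under Eligibility criteria for GP practices, "The GP practices will be randomised 1:1 and stratified by CCG using Statarand".
- **Identification.** Under Recruitment, patients are found opportunistically over a year: "The template will be triggered by either free text or Read codes relating to breathlessness". The GP then asks about contact by the study team and records yes or no.
- **Template, intervention arm.** "The electronic template will prompt the GP to action these investigations". Clinicians in these practices also receive the pathway as a laminated document, with flash cards at the workstation.
- **Template, usual care.** It "will only ask the patient for their consent to pass on contact details to the study team".
- **Screening and consent.** Under Procedure, practice staff run a weekly search to "provide a report of patients who have agreed to be contacted by the study team". The study team then screens by telephone, and written consent is taken at visit 1, where possible within a month of the consultation.
- **Comparison.** Under Data analysis, "The time to diagnosis will be analysed using survival analyses based on Cox proportional hazards survival modelling". The proportions with a valid diagnosis at 3 months and 1 year are compared by χ² tests. The analysis is described as exploratory.

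**The concern.** Randomising practices makes the practices comparable in expectation. It makes the recruited patients comparable only if recruitment works the same way in both arms. Here GP coding, asking and recording all happen after allocation, and the prompt carries more work in one arm than in the other. If that changes which patients are recruited, a difference in diagnosis between the arms can reflect who was enrolled and not what the pathway did.

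Time to diagnosis and proportion diagnosed are secondary outcomes. The study's aims include choosing the main trial's primary outcome and learning what difference would be important and realistic. A case-mix difference would carry over into that judgement. Differential recruitment is also a risk that a feasibility study is well placed to detect before the main trial, and presenting clustering as protection against bias may discourage anyone from looking for it.

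**Working it through.** The article gives no sample size, power or event count to reproduce; Outcomes says that no formal calculation is required. The check is first one of reading and then an illustration.

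**Sequence of events, from the article**

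1. The practice is allocated (Trial design; Eligibility criteria for GP practices).
2. A patient consults. The GP's free text or code fires the template (Recruitment).
3. The GP sees a template that differs by arm (Intervention). Blinding is not mentioned, but the arm-specific prompt and the laminated materials make the allocation evident.
4. The GP asks the patient and records the answer (Recruitment).
5. In the intervention arm, investigations follow within 1 month (Intervention).
6. The team screens by telephone. Consent and baseline are at visit 1, also within about 1 month (Procedure; Data collection).

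Steps 2 to 4 follow allocation and involve someone who can see it. Steps 5 and 6 share the same window, so consent and baseline may come after pathway tests. An existing diagnosis is an exclusion (Eligibility criteria for patients), so faster diagnosis in one arm could itself change who is screened in. Nothing in this sequence depends on whether randomisation was by cluster, except that clustering keeps a practice from delivering both kinds of care. That is protection from contamination.

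**Illustration of size (all inputs assumed; none is in the documents)**

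Let p_E and p_H be the probabilities of diagnosis for easy and hard causes, equal in both arms (no pathway effect), and let m₁ and m₀ be the share of easy cases among recruits. Then

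spurious difference = (p_E − p_H) × (m₁ − m₀).

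With p_E = 0.80 and p_H = 0.40 at 12 months:

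- Mix 60% v 40%: 0.6×0.8 + 0.4×0.4 = 0.64; 0.4×0.8 + 0.6×0.4 = 0.56; difference 0.08.
- Mix 55% v 45%: 0.62 v 0.58; difference 0.04.

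A second set takes p_E = 0.60 and p_H = 0.20 at 3 months, with usual care recruiting 50% easy cases (p₀ = 0.40). For n per arm and difference d = p₁ − p₀, the approximate rejection rate of the two-sided 5% χ² test is

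1 − Φ((1.96·s₀ − d)/s₁) + Φ((−1.96·s₀ − d)/s₁),

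where s₀ = √(2p̄(1−p̄)/n), s₁ = √(p₀(1−p₀)/n + p₁(1−p₁)/n) and p̄ is the mean of p₀ and p₁.

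| Easy cases, intervention arm | p₁ | d | n = 30 | n = 50 | n = 100 |
|---|---|---|---|---|---|
| 40% | 0.36 | −0.04 | 6.2% | 6.9% | 9.0% |
| 50% | 0.40 | 0 | 5.0% | 5.0% | 5.0% |
| 60% | 0.44 | +0.04 | 6.1% | 6.9% | 8.8% |
| 70% | 0.48 | +0.08 | 9.5% | 12.6% | 20.6% |
| 80% | 0.52 | +0.12 | 15.2% | 22.4% | 39.8% |

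The bias d does not shrink with sample size, so the error rate rises with n. It can take either sign. These figures ignore correlation within practices, which is a separate matter.

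**The case against.** Several stronger readings are tempting, and the article does not support them.

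- **That GPs hand-pick patients.** The template fires automatically, the GP records the patient's own answer, and the study team does the telephone screening. What remains open to influence is how the GP codes and whether and how the GP asks.
- **That refusals never reach the team.** The weekly report is a contact list. Box 1 counts eligible patients who agree to be approached against all eligible patients, Outcomes sets those consented against those identified as eligible, and reasons for declining are collated. A denominator is therefore planned. Unanswered templates and an explicit split by arm are not mentioned.
- **That recruitment will only be pooled.** Nothing says so. Box 1 relates recruitment to practice population size, and each practice belongs to one arm.
- **That both comparisons are unadjusted.** This is clear only for χ². Cox covariates may stand in an analysis plan that is not shown, and their absence from an article is no fault.
- **That a bias of 4 to 12 points is to be expected.** The figures are assumptions, and the article gives no evidence that recruitment will differ between the arms.

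It is also fair to say that the primary outcome is recruitment rate, that no effectiveness claim rests on these comparisons, and that staff interviews will explore barriers to screening and the trial's influence on usual care. All of this lowers the stakes. It does not rescue the statement that clustering minimises bias, and none of the safeguards is described as a comparison of recruited patients between arms.

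**Conclusion.** The concern holds in limited form. The strengths list claims a protection that the design does not give: clustering limits contamination, but post-allocation recruitment by GPs who can see their arm leaves identification and recruitment bias open. The χ² comparison, as stated, takes no account of case mix or of CCG, the stratification factor. That GPs know their arm is inferred from the arm-specific template and materials, since blinding is not mentioned, but the inference is hard to avoid.

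Size and direction are unknown. Under the assumed mixes above, the spurious difference is 4 to 12 percentage points in absolute size and of either sign. The consequence falls mainly on the secondary comparisons and on what is taken from them for the main trial. It does not undermine the feasibility study as such. The point merits correction because the correction is cheap and improves what the study can conclude.

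**What to change.** 1. **Reword the strength.** Claim reduced contamination, and list recruitment after allocation by arm-aware GPs as a limitation.
2. **Extend the counts already implied by Box 1 and Outcomes.** Report by arm and practice, as anonymous counts: templates triggered, marked yes, marked no, unanswered, eligible at telephone screening, and consented. Also report whether a diagnosis was recorded before consent, which the record review can supply.
3. **Compare recruits by arm on variables fixed before the consultation**, such as age, sex and previous breathlessness consultations.
4. **Replace the plain χ² with a comparison adjusted for CCG, age and sex**, and name the same covariates for the Cox model. State that this cannot remove unmeasured selection, in particular by underlying cause. MRC grade at visit 1 may already be post-intervention, so it belongs only in a sensitivity analysis.

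The cost is a few extra count fields in a search that practices already run, slightly more analysis and one reworded sentence. Patient care is unchanged.

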## Introduction

Breathlessness is associated with high healthcare use, accounting for 5% of presentations to the emergency department,^1 2^ approximately 4% of general practitioner (GP) consultations^3^ and reported by patients in 12% of medical admissions.^4^ Breathlessness is reported by around 9%–11%^5 6^ of the general population, varying with severity, socioeconomic status^6 7^ and increasing with age to 25% in people over 70 years old.^8 9^ Functional impairment from breathlessness, measured using the Medical Research Council (MRC) dyspnoea scale, is associated with reduced survival regardless of underlying diagnosis.^10^

Two-thirds of breathlessness is caused by cardiorespiratory conditions.^11^ Clinical data shows that for patients over the age of 40 the most common causes of breathlessness are chronic obstructive pulmonary disease (COPD), heart failure (HF), obesity, anaemia and anxiety.^12 13^ These conditions can be potentially diagnosed or excluded using investigations that can be performed in community settings.^12^ All of these investigations are recommended in the National Institute for Health and Care Excellence (NICE) clinical knowledge summary^14^ but there is no specific guidance on the timeframe within which they should be performed.

Primary care data have highlighted many missed opportunities over many years to diagnose conditions associated with breathlessness, such as COPD and HF,^15 16^ with many patients being diagnosed only when the disease is severe or requiring hospitalisation.^15 16^ These data indicate significant challenges in the deployment of simple diagnostics in the primary care setting. There are also well-documented misdiagnoses for COPD, asthma and interstitial lung disease across healthcare settings.^15 17–21^

Our overarching hypothesis is that a symptom-based approach for diagnosis in primary care for patients with chronic breathlessness will lead to earlier diagnosis, earlier treatment and improved outcomes such as health-related quality of life (HRQoL). However, it is also important to consider the implications of over investigating and ‘over-diagnosis’ in patients and find the balance between clinical and cost-effectiveness for a diagnostic pathway.^22^ A large and potentially expensive multicentre cluster randomised controlled trial (RCT) would be necessary to understand the clinical and cost-effectiveness of a structured diagnostic pathway for chronic breathlessness. The scope of this study is to assess the feasibility of such a trial and help inform the design.

For this feasibility study the specific aims are:

To assess feasibility by recruitment and retention rate of patients in the trial to enable calculation of the number of GP practices, cluster sizes and duration of the ultimate RCT (box 1).To better understand ‘usual care’ through prospective observation and qualitative analysis, and to understand any influence of the trial design on usual care.To determine the proposed primary outcome measure for the future trial and to increase understanding of what is an important and realistic difference while exploring potential of other outcome measures (table 1).Identify sources of data and how best to collect these in order to plan the economic evaluation that would accompany a full trial.

Box 1Feasibility measuresFeasibility measuresNumber of patients recruited per week per general practitioner (GP) practice population size.Number of participating GP practices verses the number approached.Time for GPs to screen for eligibility.Number of eligible patients who agree to be approached by the research team verses total number of eligible patients.Number and timing of investigations in the diagnostic pathway completed.Acceptability of the research visit to the participants.Data collected from interviews regarding participant experience of the trial.Data collected from interviews regarding GP experience of participating in the trial and influence on their practice.

**Table 1 T1:** Secondary outcome measures

Secondary outcome measures	Measurement tool
Proportion of diagnoses in usual care and intervention within 1 year of presentation	Review of healthcare records for all participants
Time to diagnosis	Review of healthcare records for symptom presentation and diagnosis date
Health-related quality of life	Chronic Heart Questionnaire EuroQol 5 Dimensions 5 Levels
Breathlessness	Dyspnoea−12 Multidimensional Dyspnoea Profile Medical Research Council dyspnoea scale Baseline Dyspnoea Index and Transition Dyspnoea Index
Physical activity	Activity monitors (GENEActiv and ActiGraph devices) to measure daily step count, sedentary time, moderate and vigorous activity
Exercise capacity	Incremental Shuttle Walk Test
Frailty	Short Performance Physical Battery, Fried’s frailty score, Rockwood frailty score, handgrip and quadriceps strength.

## Methods and analysis

This is a mixed methods study designed using the MRC guidelines on developing complex interventions.^23^

